**Fig. 1 Fig1:**
[figure not shown]
Study design

Reimbursement of 25 Swiss Francs for taking part in the pre-test and follow-up assessment will be offered to study participants. Consistent with prior work (e.g. [58]), participants will be able to earn credits for active participation and by fulfilling specific tasks during the intervention such as engaging with the conversational agent (maximum 8 credits per day), experience sampling measurements (3 credits per measurement occasion), weekly assessments (20 credits per assessment), and photo uploads (15 credits per upload). Participants can collect 1,000 credits in total and reach bronze status with 250 credits or more, silver status with 500 credits or more, and gold status with 750 credits or more. According to their status, participants earn tickets for the lottery (bronze status = 1 ticket, silver status = 5 tickets, gold status = 10 tickets). Participants can win 100 Swiss francs, 200 Swiss francs, and 300 Swiss francs in cash.

### Procedure

The procedure is shown in Fig. 1. After having completed the pre-test assessment, participants get instant feedback on their actual Big Five personality trait profile (BFI-2; [59]). This feedback should help participants to choose their appropriate change goal. Participants have to pick one change profile out of nine, which fits the most to their individual change goal. Each of these nine profiles explains normal characteristics of a person with high or low levels in the corresponding Big Five personality trait. To be more precise, participants can choose between nine *personality change profiles*: (1) increase in conscientiousness, (2) decrease in conscientiousness, (3) increase in extraversion, (4) decrease in extraversion, (5) increase in open-mindedness, (6) decrease in open-mindedness, (7) increase in agreeableness, (8) decrease in agreeableness, and (9) decrease in negative emotionality. For ethical reasons an intervention to increase negative emotionality will not be offered. Participant then indicate the strength of their chosen change goal on an 8-point scale from 0 = *not at all* to 7 = *totally* and their willingness to change (i.e., goal commitment and goal attainability; [60]). Additionally, participants are asked to share a link with at least three close friends, family members and their intimate partner to obtain an observer-report on the Big Five personality traits (BFI-2-S; [61]) (Table 2).

The first week of the study is an experience sampling week to measure personality manifestations in daily life (for more details, see below). The personality change intervention then lasts over 10 weeks. For each of the 10 weeks, weekly core themes will be provided (Table 1). Moreover, six different types of micro-interventions will be used in the intervention (see below). All participants are actively involved in two daily dialogues with the conversational agent. In the morning at an individually preferred time participants receive the first message for the morning dialogue and in the evening again at an individually preferred time participants receive the first message for the evening dialogue. Participants have the opportunity to read the dialogue until it is time for the next dialogue. A conversational agent will be used to remind participants to complete questionnaires, to guide them through micro-interventions, to promote commitment, to motivate participants, and to support the change process (Fig. 2). During these conversations, a combination of pre-defined answers and free-text input is used to constrain the dialog along pre-defined counselling paths and to give participants autonomy where needed (e.g., for the definition of implementation intentions in the if-then form). If participants do not actively use the PEACH app over three days, the study team will contact them via the “Support-Team Channel” (Fig. 2) and ask them whether there occurred any problems or whether they have any unanswered questions to promote adherence. After the intervention, there is a second experience sampling week and then participants are asked to answer the post-test assessment and the three-month follow-up assessment (Fig. 1). Moreover, participants were asked at post-test and follow-up assessment to share a link with their close friends, family members or intimate partners, who already provided their observer-reports at pre-test assessment, to obtain a second and third observer-report on the Big Five personality traits (BFI-S-S; [61]).

**Table 1 Tab1:** Schedule of weekly core themes and micro-interventions

Week	Weekly core theme (Source)	Brief description	Individualized implementation intention^c^	Psycho-education^b^	Behavioral activation tasks^c^	Individualized progress feedback^a^
1	Organizing a change team^d^ [27]	Participants are asked to inform 1-3 significant others such as friends or family members to talk with them about their change goals, the coaching intervention itself and to keep them updated during the intervention.	Implementation intention 1	Daily film clip or scientific input	Behavioral activation task 1	Dashboard
2	Learning from experiences by systematic reflection^b^ [17]	People are asked to analyze their own behavior and advance explanations for the resulting success or failure to learn from both. Questions that prompt self-explanations include: “How did you contribute to the performance?” or “How effective were you in the experience”. Then participants are confronted with questions such as “Consider a different approach that could have been taken.” And finally they should ask themselves: “What worked and what did not work? How will you behave in the future?”	Implementation intention 2	Daily film clip or scientific input	Behavioral activation task 2	Dashboard
3	Identifying situational/ contextual triggers^b^ [23]	Participants learn how to identify situational and contextual triggers (e.g., people, places, time in the day) that help or hinder them to show their desired behavior.	Implementation intention 3	Daily film clip or scientific input	Behavioral activation task 3	Dashboard
4	Thinking and writing about the pro’s and con’s of change^a^ [15]	Participants think about advantages and disadvantages of changing in the desired direction and of staying the same. This might eventually also enhance individual change motivation.	Implementation intention 4	Daily film clip or scientific input	Behavioral activation task 4	Dashboard
5	Learning from others by observational learning^b^ [20, 21]	Participants should look out for people in their environment, who already show their desired behavior. They analyze what these people are doing differently and try to model this behavior.	Implementation intention 5	Daily film clip or scientific input	Behavioral activation task 5	Dashboard
6	Self-reflection by means of introspection^b^ [21, 22]	Participants should watch their own thoughts and feelings when they are able to show their desired behavior and thoughts and feelings when they are not able to show the desired behavior.	Implementation intention 6	Daily film clip or scientific input	Behavioral activation task 6	Dashboard
7	Keeping a diary of strengths and resources^d^ [28]	Participants are asked to think about what they are grateful in life and about their personal strengths.	Implementation intention 7	Daily film clip or scientific input	Behavioral activation task 7	Dashboard
8	Reflecting about strengths and resources using the tree of resources^d^ [29]	Participants write down individual resources inside their tree of resources in order to visualize and reflect about personal strengths and positive aspects of life.	Implementation intention 8	Daily film clip or scientific input	Behavioral activation task 8	Dashboard
9	Thinking about the desired personality using miracle questions^a^ [16]	Miracle questions are thought experiments, which ask people to imagine their desired personality, their desired future and specific plans and their priorities for the next five years.	Implementation intention 9	Daily film clip or scientific input	Behavioral activation task 9	Dashboard
10	Looking forward and thinking about the future^d^ [30]	Participants should think about future plans, dreams, hopes, and poss	Implementation intention 10	Daily film clip or scientific input	Behavioral activation task 10	Dashboard

*Note.*
^a^Actuating discrepancy awareness; ^b^targeting thoughts and feelings to realize insight; ^c^targeting behaviors to realize practice; ^d^activate strengths and resources to realize strengths-orientation; since these general change mechanisms are overlapping in content, weekly core themes and micro-interventions might fit to more than just one general change mechanism

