### Participants and Recruitment

The targeted sample will include at least 900 German-speaking adults, who install the PEACH App on their smartphones, give informed consent, pass the screening, fill in the pre-test assessment and start with the intervention. To assure an adequate power to detect statistical significance and to demonstrate a small to medium effect of a pre-post time by group interaction we require data from 300 participants. Assuming an α error level of 0.05, a statistical power (1-β) of 0.80, and a correlation of 0.40 between the pre- and post-measurements and 75 completers for each group, we would be able to detect a small effect of Cohen’s *d* = .22. Computing power for repeated measures, which is the case in this study, is more complex. As such, this power analysis only gives a rough idea of the effect sizes the study could reasonably detect. In a similar study [33], 67% of participants completed the post-test survey after 6 weeks, from a cohort of 273 who started the intervention. Based on this estimate and taking the longer duration of this study into account, we expect even more attrition. Should drop-out rates be higher than expected, we may recruit additional participants to ensure sufficient statistical power. To be eligible for the study, participants must be: (1) 18 years or older; (2) able to read German; (3) not in a psychotherapeutic or psychiatric treatment; (4) owner of a smartphone (Android or iOS) with mobile internet connection; and (5) interested and motivated to participate at the intervention and to change some aspects of their personality. The focus of this intervention study is explicitly on healthy adults. Thus, adults with mental health disorders and other psychosocial problems will be excluded. Participants will complete an online eligibility screening that checks for the inclusion criteria. Excluded candidates with mental health disorders and psychosocial problems will be provided with an information and contact details of the psychological counseling service of the University of Zurich.

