#### Outcome assessment

##### Self-reports

The self-reports include a pre-test, a post-test and a three-month follow-up assessment. Pre-test assessment will take place before the intervention, post-test assessment after the intervention and the follow-up assessment three months after the end of the intervention to check whether personality changes could be maintained over a longer period of time or revert over time. At all points of measurement participants will be automatically directed from the PEACH app to the online survey tool (limesurvey.org) to answer all questionnaires on the smartphone (Fig. 3). The main outcome assessment includes the Big Five Inventory 2 (BFI-2; [59]) to assess the Big Five personality traits and trait-related facets. Further outcome variables and control variables are willingness to change [60], implicit theory of personality [64], satisfaction with life (SWLS; [65]), satisfaction with life domains [2], and self-esteem (RSES; [66]) (Table 2).

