### Data Analyses

Longitudinal multilevel modeling (MLM) and structural equation modeling (SEM) will be used to analyze the (intensive) longitudinal, nested data structure and change over time [81–84]. Both data-analytic methods are specifically suitable to model change explicitly as a function of time and can be used to formulate equivalent models, providing identical estimates for the collected data. Separate models will be analyzed including the outcome assessments at pre-, post- and follow-up (self-reports and observer-reports), daily diary assessments, and weekly self-report assessments. Predictor/control variables will be added to the models to examine how individual growth will be moderated by variables such as intervention condition, change goal or willingness to change. The statistical modeling programs Mplus [85], and updated R packages (R Core Team, Vienna Austria) will be used to estimate the growth curve models.

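### Neither the main outcome nor the power statement is tied to the one trait and direction that each participant chooses to change

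*Protocol article*

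**What the plan says.** Under Procedure, each participant selects a single target after seeing feedback on the pre-test profile: "Participants have to pick one change profile out of nine, which fits the most to their individual change goal". Conscientiousness, extraversion, open-mindedness and agreeableness are each offered in both directions. Negative emotionality is offered only as a decrease.

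Under Outcome assessment, Self-reports: "The main outcome assessment includes the Big Five Inventory 2 (BFI-2; [59]) to assess the Big Five personality traits and trait-related facets". No score relative to the chosen goal is defined there. The hypothesis in Research Goals and Hypotheses is greater trait change than on the wait-list, without naming the chosen trait or a direction.

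Under Participants and Recruitment, the powered test is "a small to medium effect of a pre-post time by group interaction". Its inputs are: "Assuming an α error level of 0.05, a statistical power (1-β) of 0.80, and a correlation of 0.40 between the pre- and post-measurements", with "75 completers for each group"; hence "we require data from 300 participants" and "we would be able to detect a small effect of Cohen’s *d* = .22". No trait or score is named. The same section describes the calculation as rough.

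Under Data Analyses: "Predictor/control variables will be added to the models to examine how individual growth will be moderated by variables such as intervention condition, change goal". Progress relative to the goal is scored in one place only, the dashboard traffic light (Technological Background of the Intervention). That uses daily personality states, not the BFI-2.

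**The concern.** For any one trait, most participants may not be trying to change it, and those who are may be pulling in opposite directions. A condition effect on that trait across everyone averages positive, negative and null targets. Splitting by goal avoids the averaging but leaves small cells and a three-way contrast.

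The two-way power statement describes neither analysis. It fits only a single score that means the same thing for every participant, and the article does not define one. An intervention that works as intended could therefore show little on the trait-level tests. The choice among traits, facets and profiles would also stay open until results are known.

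**Working it through.** **1. The plan's own figure.** Inputs from Participants and Recruitment: N = 300, four groups of 75, α = 0.05, power 0.80, r = 0.40. For a repeated-measures within-between interaction with two time points:

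- λ = f² × N × 2 / (1 − r), with 3 and 296 degrees of freedom.
- 80% power needs f = 0.105 (λ = 0.1051² × 300 × 2 / 0.6 ≈ 11.05).
- d = 2f = 0.21.

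The printed 0.22 follows if f is first rounded to 0.11, which is my inference; f = 0.11 gives power 0.84. So the figure is approximately reproduced, as an omnibus four-group test with equal groups.

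**2. The experimental versus wait-list contrast at N = 300.** Recruitment is 2:1, so take 200/100. The factor for 80% power at two-sided 0.05 is 1.96 + 0.84 = 2.80, and √(1/200 + 1/100) = 0.1225.

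- ANCOVA: SE = √(1 − 0.40²) × 0.1225 = 0.9165 × 0.1225 = 0.112; detectable d = 2.80 × 0.112 = 0.31.
- Change score: SE = √(2 × 0.60) × 0.1225 = 1.095 × 0.1225 = 0.134; detectable d = 2.80 × 0.134 = 0.38.

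**3. One trait across all participants.** Assume every participant moves d in the chosen direction and not at all on other traits:

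net effect = d × (share up − share down)

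The article gives no goal shares, so these are assumptions. Take 25% up and 3% down (net 0.22) and d = 0.35, with 200/100 and ANCOVA. Power = Φ(δ/SE − 1.96); the opposite tail adds less than one percentage point.

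- Goal-signed score: δ = 0.35; 0.35 / 0.112 = 3.12; power = Φ(1.16) = 0.88.
- Unsigned trait: δ = 0.35 × 0.22 = 0.077; 0.077 / 0.112 = 0.69; power = Φ(−1.27) = 0.10.

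A larger sample does not rescue it. With all 900 analysed (600/300, change score) and d = 0.22:

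| Net share on the trait | Net d | Power |
|---|---|---|
| 1 (goal-signed) | 0.220 | 0.81 |
| 0.30 | 0.066 | 0.13 |
| 0.20 | 0.044 | 0.08 |
| 0 (equal up and down) | 0 | α |

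**4. The change-goal moderator.** Suppose 20% choose a given profile. The condition effect within that profile then has:

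- N = 300, 40/20: change score 2.80 × 1.095 × √(1/40 + 1/20) = 0.84; ANCOVA 0.70.
- N = 900, 120/60 (no dropout): change score 2.80 × 1.095 × √(1/120 + 1/60) = 0.49; ANCOVA 0.41.

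All four are well above 0.22.

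**The case against.** The strongest reply is that this is a condensed article. Outcome coding and the way traits are combined may be set out in an analysis plan that is not shown, and the power calculation is openly called approximate. Data Analyses also names change goal as a moderator, so opposite-direction effects can be estimated. That much stands, and it rules out three stronger readings that a reader might infer.

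- *Effects will cancel.* The article never says that unsigned scores will be pooled over goals. Full cancellation would need equal up and down shares, which are not given. It cannot happen for negative emotionality, which is offered in one direction and can only be diluted.
- *The powered test does not exist.* It does: a time-by-group interaction is stated and can be run. What is missing is the score it applies to.
- *Testing many traits, facets and informants inflates false positives.* Nothing says that each is tested at an uncorrected 0.05, and multiplicity can be handled in an analysis plan. It is a separate matter.

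The reply does not remove the mismatch. The article itself states a hypothesis, a main outcome, a powered test and a model, and the power statement fits neither analysis that these allow. Calling it rough covers imprecision, not a different contrast.

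**Conclusion.** The point holds in limited form: the main outcome and the power statement are not tied to the chosen goal.

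On one trait across all participants, power falls to about 10%, against about 88% for a goal-signed score. Through the goal moderator, the detectable effect within a 20% profile is about 0.5 to 0.8 on change scores, not 0.22.

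The exact sizes rest on assumptions that the article does not supply: goal shares, d = 0.35, no movement on unchosen traits, and 200/100 as the split of the 300 completers. The direction is less sensitive: at d = 0.22 with all 900 analysed, power is about 13% or less at every net share up to 30%. This should be corrected before analysis; it does not invalidate the design.

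**What to change.** - **Primary outcome.** Use the score on the participant's chosen trait, standardised and signed so that positive is the desired direction.
- **Model.** Fit one model over all nine profiles with a single experimental versus wait-list contrast, adjusted for the signed pre-test score and profile.
- **Comparison period.** Estimate the contrast over the first four weeks. The Design section leaves the wait-list untreated only then, and afterwards gives it the same intervention. The repeated trait measure in that period is the weekly BFI-2-S; Table 2 schedules the full BFI-2 self-report only at pre-test, post-test and follow-up. Because goals are chosen after seeing pre-test scores, signed change can partly reflect regression to the mean, so interpret it only as a difference from the untreated wait-list.
- **Power.** Restate the detectable effect for this contrast under 2:1 allocation: about 0.31 with ANCOVA or 0.38 with change scores at 200/100 and r = 0.40. The article assumes that correlation for pre- and post-measurements, so say whether it is kept for four weeks.
- **Secondary.** Keep trait-, profile- and facet-specific effects, and the pre/post/follow-up BFI-2 growth models.

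The cost is a recoding step, revised wording and a new power sentence; no new data are needed. There are two limits: the primary estimate averages over traits, and it reflects the early part of a 10-week programme.

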**Fig. 2 Fig2:**
[figure not shown]
The PEACH App and its Components. *Note.* Chat-based interaction with the conversational agent PEACH (left), the sidebar (middle) that allows participants to switch to either a dashboard with a personalized overview of the current status of the intervention (right), a media library used for psychoeducational video clips, a chat channel that allows participants to communicate with the “Support-Team”, or a page for frequently asked questions about the PEACH study and the app

### Weekly Core Themes and Micro-Interventions

The structure of the PEACH intervention includes (a) weekly core themes with specific micro-interventions and (b) micro-interventions that are not directly related to the weekly core themes. The weekly core themes and the micro-interventions that were used every day for 10 weeks are shown in Table 1. In the following, we briefly discuss the six types of micro-interventions that were used in PEACH: (1) individualized implementation intention, (2) psychoeducation, (3) behavioral activation, (4) self-reflection, (5) resource activation, and (6) individualized progress feedback. The included micro-interventions were selected to target and to activate the general (common) change mechanisms in order to maximize the effects of the intervention [7].

#### Individualized implementation intentions

An implementation intention is a self-regulatory strategy in the form of an “if-then plan” that can lead to better goal attainment [5, 24]. This micro-intervention targets the general change mechanism *targeting behaviors to realize practice.* Participants generate one individual and specific implementation intention based on suggested behavioral activation task every Sunday. This individually built implementation intention should be implemented in daily life during the following week as often as possible. Examples for implementation intentions are: “If I have to work concentrated, then I switch into flight mode” (Productivity, Conscientiousness), “If I have no meetings before 1:00 p. m,, then I will go to the gym.” (Productivity, Conscientiousness) or “If I see something beautiful, then I will take a photo.” (Aesthetic Sensitivity, Open-Mindedness).

#### Psychoeducation

Psychoeducation fosters knowledge transfer about personality dispositions, personality change and its outcomes. This micro-intervention operationalizes the general change mechanism *targeting thoughts and feelings to realize insight.* In the present coaching intervention, participants receive every morning either a short film clip or a message with scientific “food for thought”. In total, we developed 36 film clips (11 film clips providing information about personality dispositions and personality change in general and 5 film clips for each participant fitting to the chosen change goal and its outcomes) and 104 scientific messages (34 providing input about personality dispositions and personality change in general and 10 messages for each participant fitting to the chosen change goal). Film clips provide worst- and best-case scenarios and scientific facts about the advantages of achieving the desired change. These interactive elements should also promote motivation and adherence among participants.

